#### MRI data collection and quality control

MRI will be performed at an accredited facility, by fully trained and qualified personnel at the Royal Hobart Hospital. MRI will be conducted according to the MRI technologist manual for the study. ~20 scans will be performed at each MRI visit, with acquisition sequence - 3D FLAIR, 3DT1, MT on/off, qT1 map and DTI (minimum 32dir). To ensure sufficient quality for analysis (e.g. no movement artefacts), baseline MRI images will be checked by MRI analysts prior to commencing the intervention/ first participant visit, and repeated if necessary. The same quality evaluation will be completed on post-intervention MRI scans. At all stages of the manual, semi-automated and automated analyses of MRI scans, output will be examined by an expert observer (trained clinical trial research assistants, medical doctors and/or clinical neuroimaging specialists) with supervision from Sydney Neuroimaging Analysis Centre (SNAC) directors / image analysis specialists. Where consensus cannot be reached for discrepancies found between analysts, the SNAC Director will make the final determination.

#### MRI image pre-processing for analysis

Prior to the calculation of MRI volumetrics, 3D T1-weighted images will be preprocessed using in-house brain-extraction and lesion-filling tools with manual quality assurance and correction where needed. Brain tissue volumes (whole brain, white matter, grey matter, peripheral (cortical) grey matter, ventricular cerebrospinal fluid), normalised for subject head size, will be estimated at each time point using the SIENAX [26], part of FSL-FIRST methods [27]. Lesion numbers and volumes will be calculated from manually drawn lesion masks on baseline 3D-FLAIR images. Lesion masks will be transformed to follow-up 3D T1-weighted image space and adjusted for lesion activity (see ‘Lesion assessment’ below) by trained analysts.

#### Lesion assessment

A T2-weighted lesion will be identified as a rounded or oval area of hyper-intensity, according to the guidelines by Filippi et al. [40]. A lesion will only be counted once per scan. If a lesion extends across more than one slice, it is only counted once, rather than counting the number of lesions per slice. A lesion will be considered “new” if it was present at the post-intervention MRI and not at baseline. Lesions that are adjacent to a pre-existing lesion but connected to it by a relatively low signal area will also be considered new. Lesions >5mm will be classified as “enlarged” if the lesion size has either increased by at least 100%, or the size has increased in at least two consecutive slices. Lesions <5mm in size must satisfy both criteria to be classified as enlarged.

#### Advanced MRI metric assessments

The diffusion tensor model is fitted to the pre-processed data using FSL-DTIFIT. Magnetisation transfer ratio maps are generated as magnetisation transfer-On image (MTon), co-registered to magnetisation transfer-Off image (MToff) by linear registration. Magnetisation transfer ratio is calculated in voxel-wise fashion as MToff subtract MTon, divided by MToff. Quantitative T1 mapping will be obtained by processing the variable flip-angle spoiled gradient recalled echo data with QUIT open-source software [41]. A map of the longitudinal relaxation time (T1) is generated by linear least-squares fitting of the signal intensity curve as a function of flip angle at constant transfer ratio.

#### Participant-reported MS symptom assessments

Questionnaires will be collected directly into eCRFs via REDCap, minimising transcription errors and missing data (refer to data management section). Paper format questionnaires will be provided to participants if requested.

#### Hospital Anxiety and Depression Scale (HADS)

Fourteen-item questionnaire (7 anxiety items, 7 depression items) with high reliability (test-retest ICC = 0.83; Cronbach’s alpha >0.8) and good criterion validity, with high correlations with other measures of depression and anxiety [29, 30]. Scores ≥8 on each subscale indicate clinically important depression and/or anxiety symptoms and, above this cut-off score, a change of ≥2 points is considered to be clinically meaningful [29]. Use licensed by GL Assessment, MAPI Research Trust, available from GL Assessment [42].

#### Assessment of Quality of Life-8 dimension (AQoL-8D)

The AQoL-8D is a 35-item questionnaire that will assess physical and psychosocial quality of life across 8 dimensions: Independent Living, Senses, Pain, Mental health, Happiness, Self-worth, Coping and Relationships. The AQoL-8D has good test-retest reliability (intraclass correlation coefficient (ICC) = 0.7) and good convergent and predictive validity, as assessed by a multi-instrument comparison study [31]. AQoL-8D has been validated for use in people with MS. [43] Data collection forms and STATA/ SPSS scoring utility algorithm and user manual, and guides for interpreting the clinical importance of subscale difference scores, are available online from [44]. Use registered on 30 May 2020.

#### Fatigue Severity Scale (FSS)

The FSS is a nine-item questionnaire which measures fatigue symptom severity on a seven-point ordinal scale [30, 32]. In an MS population, the FSS has good reliability (ICC = .76, over 6 months) and good-excellent validity metrics (see [45]). A difference of at least 0.45 points is considered a clinically significant change in fatigue [46]. Forms and scoring instructions are available online from [47].

#### Floodlight Open

We will use selected metrics from the battery of tests completed via the Floodlight Open smartphone app [48]. We have selected only the Floodlight metrics with published reliability and validity assessments (e-SDMT, Pinching test, Draw a shape test and U-Turn test) [33]. We may update inclusion or exclusion based on further assessments and validation available at the time of analysis.

#### e-SDMT

Participants will be instructed to match as many pairs as possible in 90 s, by pressing the digit on the onscreen keypad corresponding to the symbol displayed, according to the legend assigning a symbol to each number between 0 and 9. Number of correct matched pair responses has good retest reliability for people with MS (ICC = 0.85) and good concurrent validity (Spearman’s rank correlation with the oral SDMT, *ρ* = 0.85) [33]).

#### Pinching test

Participants will be instructed to use their index and thumb in a pinch-grip to ‘squeeze’ as many on-screen tomatoes as possible within 30 s, and perform each pinch as fast as possible. We will analyse the number of successful pinches, which has moderate retest reliability (ICC = 0.72) and moderate concurrent validity, based on correlation with the 9 hole peg test performance (*ρ* = −0.52), which is the standard manual dexterity assessment used in people with MS. [33]

#### Draw a shape test

Participants will trace the line of 6 shapes, in the direction indicated by an arrow, as quickly and accurately as possible. Each shape is drawn twice, but only the better tracing is used for analysis of tracing error (Hausdorff distance). This test has good retest reliability ICC = 0.85 and moderate correlations with the 9-hole peg standard dexterity test [33]. We will also analyse normalised Hausdorff distances for the 3 curvilinear shapes (spiral, figure-8, circle), which reportedly have greater discrimination between healthy controls and people with MS compared to straight line shapes [49]. Participants will be instructed to use the same hand for all three timepoints in this study for both the pinching test and the draw a shape test.

#### U-turn test

Participants will be instructed to walk at their normal pace between two points 2–4 m apart and complete at least 5 walking turns within 60 s, with their phone in their front or back hip pocket. Mean U-turn speed has good retest reliability (ICC = 0.83) and moderate concurrent validity (correlation with the timed 25-foot walk standard clinical measure, *ρ* = −0.52) [33].

The Floodlight Open smartphone app can be downloaded from Google Play for Android or Apple store for IOS. At the time of writing, the Floodlight Open app is available but will be replaced by Roche Floodlight MS app in the future.

### Plans to promote participant retention and complete follow-up {18b}

If a participant misses more than 3 consecutive intervention visits, they will be considered protocol non-compliant. These participants will be permitted to continue in the study until the end of the 5-week intervention phase, and remain in the study to complete follow-up safety and PROMs, but will be excluded from the follow-up MRI. Outcome measures are collected at the final intervention visit (face to face) and then again 4 months after group allocation. An automatic email is sent to remind participants to complete PROMs via REDCap. Additionally, participants will be contacted three times by two different methods before they are considered ‘lost to follow up’.

Protocol deviations will be monitored monthly by the trial management group and appropriate corrective and preventative actions taken to reduce incidence of protocol deviations. The statistical analysis plan will include per protocol analysis and intention to treat analysis for AE and participant-reported outcomes. As the follow-up MRI will only be conducted for participants without substantial protocol deviations, intention to treat analysis is not possible.

### Data management {19}

REDCap will be used to manage the research data. REDCap is an open source, free, mature, secure web application for building and managing online surveys and databases. It is a robust system for research data management, supporting participant tracking, randomised group allocation, web-based questionnaires, separation of identifying and clinical data and tracking/auditing of data changes. REDCap is fully compliant with good clinical practice (GCP) guidelines, and international standards for clinical trial data management. All research staff will complete training in REDCap prior to entering live study data.

All participant-reported data will be collected directly to eCRF, minimizing transcription errors and missing data. Data validation rules will be used to query potential data errors. All screening and enrolment data will be quality assessed by a second member of the team prior to clinical PI sign off and confirmation of eligibility for group allocation. Clinical PI sign off will be required for all AEs and participant withdrawals. If participants request a paper questionnaire be provided, this will be printed from REDCap and then entered by study personnel at a later date. Quality control will be performed on all data that is not directly entered. Source data verification will be performed against the digital medical record (DMR) for demographics, MS diagnosis, MS type, MS history, MS relapses, MS treatments, EDSS score, general medical history, symptoms and concomitant medications.

The MRI data will be analysed at SNAC and the Menzies Institute for Medical Research, Hobart, according to a pre-defined data dictionary and analysis plan. All MRI scans will be codified and transmitted to SNAC via a secure web portal, according to the MRI transfer manual, for central analysis.

Cognitive and motor assessment data will be directly entered by participants into the Floodlight app. Participants will consent to share their Floodlight ID to enable access to this data from the Roche open access data portal [48]. This data will be downloaded in CSV format and integrated with the study datasets. Floodlight data is stored on Amazon Cloud and data managed by F.Hoffmann La-Roche Ltd.

### Confidentiality {27}

Data will be collected, handled and stored in accordance with GCP guidelines [50], The Privacy Act (1988) [51] and the Australian Code for the Responsible Conduct of Research, 2018 [52]. A data management plan outlining the collection, handling, storage, security, access controls and archiving of study data will be developed in accordance with the sponsor Management of Research Data Procedure.

Identifiable data (name, address, phone number, email, sex, date of birth, emergency contact and emergency phone number, neurologist name and neurologist phone number) collected during screening will not leave the study site. Each participant will be given a unique, pseudonymised participant identifier number that will be used on all case report forms and stored separately from their identifiable data. The participant ID will be assigned sequentially.

Trial data will be made available to suitably qualified members of the study team, monitors and auditors, HMHREC and TGA as far as required by law. Study records will be archived for a minimum of 15 years following study completion, in line with sponsor requirements and Good Clinical Practice guidelines.

Consent will be sought from participants to allow MRI and clinical data to be retained indefinitely and made available for future ethically approved research by us and external collaborators with appropriate confidentiality and data sharing agreements in place.

### Plans for collection, laboratory evaluation and storage of biological specimens for genetic or molecular analysis in this trial/future use {33}

N/A.

## Statistical methods

### Statistical methods for primary and secondary outcomes {20a}

The methods of analysis will be detailed in a statistical analysis plan and signed off by the CI prior to data lock and data analysis taking place.

#### Primary outcome—adverse events

A Fisher’s exact test will be used to compare the proportions of people in sham vs. rTMS who experience any treatment-emergent AEs. If different categories of treatment-emergent AEs are reported, we will run additional tests to compare proportions of AEs of each severity level (treatment emergent AEs, high intensity AEs, SAEs and SUSARs).

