**Discussion:**

This study will determine whether this rTMS protocol is safe and tolerable for people with MS. MRI and participant-reported symptom assessments will serve as preliminary indications of rTMS efficacy for myelin addition to inform further studies.

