### Outcomes {12}

#### Primary outcomes

The primary outcome will be the incidence of treatment emergent adverse events (AE) and serious adverse events (SAE), recorded at each visit during the intervention phase. Incidence will be compared between rTMS and sham using the proportion of participants that had at least one AE against participants who experienced no AEs (each participant counted once). AEs leading to premature discontinuation from the study intervention and serious treatment-emergent AEs will be presented either in a table or a listing. A clinically acceptable difference between the rTMS and sham conditions in treatment emergent events is 10% for adverse reactions and 0% for suspected unexpected serious adverse reactions (SUSARs). We defined this clinically acceptable difference based on previously reported rates of the most common side effects in sham-controlled rTMS clinical trials for depression, which were headache (mean incidence rates of 16% sham vs. 28% rTMS; 12% difference) and scalp pain/discomfort (mean incidence rates of 15% sham vs. 39% rTMS; 24% difference) [25]. Clinical trials using rTMS for depression typically deliver higher intensity and longer duration stimulation, so we expect lower incidence rates of these common adverse reactions. Risk of serious adverse reactions is reduced by excluding participants who are potentially at higher risk of serious adverse reactions to rTMS (e.g. history of seizure) [14, 15].

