### Sample size {14}

Thirty participants in total will be recruited. The sample size of 30 participants has been selected based on the safety and exploratory nature of the study.

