#### AE severity assessment

Grade 1—Mild, asymptomatic or mild symptoms, clinical or diagnostic observations only; intervention not indicated.

Grade 2—Moderate, minimal, local or non-invasive interventions indicated; limiting age-appropriate instrumental activity of daily living (ADL)

Grade 3—Severe or medically significant but not immediately life threatening; hospitalisation or prolongation of hospitalisation indicated, disabling, limiting self-care ADL

Grade 4—Life threatening consequences; urgent intervention necessary

Grade 5—Death related to AE

Adverse reactions are those AEs that are deemed by the clinical PI to be related to the study intervention.Related—The AE is known to occur with the study intervention, there is a reasonable possibility that the study intervention caused the AE, or there is a temporal relationship between the study intervention and event. Reasonable possibility means that there is evidence to suggest a causal relationship between the study intervention and the AE.Not related—There is not a reasonable possibility that the administration of the study intervention caused the event, there is no temporal relationship between the study intervention and event onset, or an alternate aetiology has been established.

A serious adverse event (SAE) is defined as any untoward occurrence that;Results in deathIs life threateningRequires hospitalisation or prolongation of existing hospitalisationResults in persistent of significant disability or incapacityConsists of a congenital abnormality or birth defectIs otherwise considered medically significant by the investigator

*Expected AEs:* (common but usually resolve soon after rTMS cessation): Headache; dizziness; tingling of fascial muscles; scalp discomfort.

*Expected SAEs:* admission to hospital for elective surgery; MS relapse; MS disability progression.

Safety oversight will be provided by an independent neurologist, free from the study conduct, who has declared that they are free from conflicts of interest. They will review SAEs and reactions to confirm severity, causality and relationship. A review will be conducted within 3 to 7 days of the event.

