## Trial status

Active, Version 5_01 November 2021. First participant recruited Jan 2021. Twenty participants recruited as of October 2021. Expected last participant, last visit by end December 2021. We originally planned to recruit 30 participants; however, due to restrictions related to the COVID-19 pandemic, the study timeframe was truncated. To meet funding-related timelines, recruitment has now been closed at 20 participants. The protocol manuscript was not submitted earlier because recruitment was previously planned to continue to reach 30 participants. At submission, no data have been statistically analysed for intervention comparisons.

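### The primary Fisher's exact test does not assess the plan's 10-point margin: it tests no difference, on all-cause AEs, while the margin is set on adverse reactions

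*Protocol article*

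**What the plan says.** The primary objective is to determine whether the intervention is safe and tolerable, and the Abstract's Discussion says: "This study will determine whether this rTMS protocol is safe and tolerable for people with MS".

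Under Primary outcomes, two things are fixed:
- The comparison: "Incidence will be compared between rTMS and sham using the proportion of participants that had at least one AE". Each participant counts once.
- The limit: "A clinically acceptable difference between the rTMS and sham conditions in treatment emergent events is 10% for adverse reactions and 0% for suspected". The sentence ends by applying the 0% to SUSARs, the serious related events that were not expected.

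The section on AE severity assessment defines the endpoint that carries the 10%: "Adverse reactions are those AEs that are deemed by the clinical PI to be related to the study intervention". The Assessing section under Adverse event reporting and harms defines an AE more widely, to include occurrences unrelated to the intervention.

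Under Statistical methods, the primary analysis reads: "A Fisher’s exact test will be used to compare the proportions of people in sham vs. rTMS who experience any treatment-emergent AEs". Further tests are planned by severity level: treatment-emergent AEs, high-intensity AEs, SAEs and SUSARs. Adverse reactions are not in that list. The article does not say how the 10% will be judged.

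On size, the Sample size section says "Thirty participants in total will be recruited", with no power or precision calculation. Trial status reports that "recruitment has now been closed at 20 participants".

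**The concern.** The limit and the test differ in two ways.

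1. **Hypothesis.** Fisher's exact test asks whether the data contradict equal proportions. The margin asks whether the excess on rTMS is at most 10 points. Not rejecting the first does not answer the second, least of all in a small trial.
2. **Endpoint.** The margin is set on related events. The test is run on events of any cause, and no listed comparison uses related events only.

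The stake is the primary objective. The plan says in advance how much excess harm is acceptable, then names a primary test whose result, either way, does not say whether that limit was met.

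**Working it through.** **Inputs from the Protocol article.** Margin 10 points; alpha 0.05; planned arms 20 and 10; recruitment closed at 20; allocation 2:1.

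**Assumptions.** The test is two-sided, since sidedness is not stated. The arm split at N=20 is not given, so 14/6, 13/7 and 12/8 are shown. Any-AE rates are not given, so sham rates from 5% to 50% are used. The sample size of 30 has no statistical inputs, so there is no planned power figure to reproduce.

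**Step 1. Power at a true 10-point excess.** Power is the sum, over all rTMS counts i and sham counts j, of Bin(i; n1, p1) × Bin(j; n2, p2) wherever the Fisher p-value is below 0.05.

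| Sham v rTMS | 20/10 | 14/6 | 13/7 | 12/8 |
|---|---|---|---|---|
| 5% v 15% | 0.4% | 0.1% | 0.1% | 0.4% |
| 10% v 20% | 1.4% | 0.3% | 0.5% | 1.1% |
| 15% v 25% | 2.8% | 0.7% | 1.1% | 2.0% |
| 20% v 30% | 4.1% | 1.3% | 1.7% | 2.7% |
| 30% v 40% | 5.2% | 2.9% | 2.5% | 3.5% |
| 50% v 60% | 5.0% | 5.1% | 3.1% | 3.5% |

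An excess exactly at the margin would be non-significant about 95% of the time or more.

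**Step 2. What reaches significance.** At 20/10 with no sham events, 8/20 is needed (40 points, p=0.029). With 2/10 on sham, 14/20 is needed (50 points, p=0.019). With 8 or more of 10 sham participants having an event, no excess can be significant.

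**Step 3. A worked result.** Take 8/20 (40%) against 2/10 (20%), a difference of 20 points. Fisher gives p=0.42. The Wilson limits are 21.9% to 61.3% on rTMS and 5.7% to 51.0% on sham. The Newcombe limits follow:
- lower: 0.20 − √[(0.400 − 0.219)² + (0.510 − 0.200)²] = −0.16
- upper: 0.20 + √[(0.613 − 0.400)² + (0.200 − 0.057)²] = +0.46

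The p-value is far from significance, and the interval allows excesses well above 10 points.

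**Step 4. Can an interval meet the margin at this size?** With no events in either arm, the Newcombe upper limit is 16.1 points (20/10) or 22.8 points (13/7), both above 10. But 0/20 against 1/10 gives −0.10 + √[0.161² + (0.100 − 0.018)²] = 8.1 points, and 0/13 against 2/7 gives 2.0 points. With no true difference and rates from 5% to 50%, the upper limit falls below 10 points in 8% to 18% of trials at 20/10 and in 2% to 15% at N=20.

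**Step 5. Size of a powered margin test.** With 2:1 allocation, equal true rates p, one-sided 0.025 and 80% power, sham n = (1.96 + 0.84)² × 1.5 × p(1 − p) / 0.10². At p = 16% this is 7.85 × 1.5 × 0.1344 / 0.01 ≈ 159, so 477 in total. At 10% the total is 318, and at 50% it is 885. A powered margin test is out of reach, so the remedy has to be estimation.

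**The case against.** **Detail may sit in the analysis plan.** The article defers detailed methods to a separate plan, which may contain an interval or use the margin. That is fair as far as missing detail goes. It does not remove a conflict between two things the article itself fixes: the test with its endpoint, and the margin with its endpoint.

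**The terms may be used loosely.** The margin sentence also speaks of treatment-emergent events, so adverse reactions might mean AEs in general. The article's own definitions point the other way, and on the loose reading the mismatch of hypothesis remains.

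**Low power is no fault in phase 1.** This stands. The trial is declared a safety and exploratory study. The power figures show only how little the test says about the margin.

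Some stronger readings are tempting, but the documents do not support them:
- *A non-significant result will be declared safe.* The article nowhere says so. Safety review also includes tables or listings of discontinuations and serious events, severity grading by a clinician blind to allocation, and independent neurologist review of SAEs.
- *The 10-point margin cannot be shown.* Step 4 gives tables where it is. Unlikely is the right word.
- *The test would miss any harm.* At 66% against 16%, power is 67% at 20/10 and 41% at 13/7.
- *Power can be read from the cited headache and scalp-discomfort rates.* Those are single-symptom rates from depression trials, and the article expects lower ones here. They are not any-AE rates.
- *The SUSAR limit has the same defect.* SUSARs are among the listed comparisons, and a 0% criterion can be checked by counting.
- *The reduced sample size is concealed.* Trial status discloses it openly.

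**Conclusion.** The point holds as a mismatch of test, endpoint and threshold. The 10-point limit on adverse reactions is not assessed by the stated primary test, and a non-significant result would carry little information about it: at a true excess equal to the margin, power is about 0.4% to 5% at 20/10 and 0.1% to 5.1% at N=20. This rests on a two-sided test, assumed sham rates of 5% to 50%, and an assumed split near 2:1. The two mismatches themselves rest only on the article's wording and need no assumed rate. The conclusion goes no further than this: it does not say that the trial will misreport safety, or that it should have been larger.

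**What to change.** - Make the main safety comparison the rTMS-sham risk difference in participants with at least one adverse reaction, with a Newcombe or exact 95% CI shown against the 10-point margin.
- Report any treatment-emergent AE in the same way, as supportive. Fisher p-values can stay as description.
- Report SUSARs as counts per arm with an exact upper bound. For zero events the one-sided 95% bound is 1 − 0.05^(1/n): 13.9% for n=20, and 19% to 22% for 12 to 14 participants on rTMS.
- State that a non-significant Fisher p-value is not evidence that the difference lies within the margin, and that at this size the trial is unlikely to show that it does.
- As a minor point, carry the closure at 20 and the actual split into the analysis and its stated precision.

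The cost is wording and a few lines of analysis. The relationship of each AE to the intervention is already recorded, so no new data are needed. Trial status says that no intervention comparison had been analysed at submission, so the change could have been made before results were seen. The downside is that the safety conclusion becomes an estimate with wide limits, which is weaker than the article's claim to determine safety.

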## Assignment of interventions: allocation

### Sequence generation {16a}

After confirming study eligibility, participant allocation to rTMS or sham will be performed automatically using REDCap software. We will use an allocation ratio of 2:1, with twice as many participants allocated to the active rTMS group as sham control, stratified by sex and a block size of 6.

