#### Secondary outcomes

##### Protocol compliance

We will use a Fisher’s exact test to compare sham and rTMS proportions of participants that are compliant (complete all 20 sessions within the time frame) vs. non-compliant (fail to complete all sessions within the time frame).

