##### MRI

Proportion of participants with new lesions or enlarging lesions at the post-intervention time point will be compared between sham and rTMS using a Fisher’s exact test. Continuous MRI measures will be analysed with full factorial mixed MANOVA [within-subjects factor: time (baseline, post-treatment); between-subject factor: intervention group (rTMS, sham)], examining main effects and time*treatment interaction. If assumptions of MANOVA are violated when analysing combined MRI measures (e.g. items too highly correlated; Box’s test violated), we will split up the analyses into variable sets by tissue type and region (e.g. whole brain, lobe-specific measures separated). We may use deidentified data from publicly available MRI databases, including healthy control participants, in preliminary analyses to inform variable sets in multivariate analyses and to aid interpretation of results.

We will follow up MANOVA(s) with canonical discriminant analysis to examine rTMS/sham group separation on the linear combination of measures of myelin. We will also run univariate mixed-ANOVAs on measures of total myelin content, to examine the simple effects of intervention group at the post-intervention time point, as detailed a priori in the statistical analyses plan. False positives from multiple comparisons will be controlled using the false discovery rate (FDR) procedure [53] with threshold set at the conventional 5% level.

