##### Participant-reported questionnaire and Floodlight data

Continuous outcomes (AQol8D, HADS, FSS, U-Turn speed and Draw a Shape tracing error) will be compared between rTMS and sham conditions with univariate mixed-ANOVAs, as described above for MRI. Significant time by intervention interactions will be followed up with simple effects tests, comparing rTMS to sham group means within each time point.

Outcomes with count data (e-SDMT, Pinching, tracing error in the Draw a Shape test) will be analysed using Mann-Whitney *U* test to compare medians between rTMS and sham groups within each time point. The time by intervention interaction will also be examined using Mann-Whitney *U* tests on within-subject change from baseline, separately for the post-intervention and follow-up timepoints, controlling for false positives using FDR set at 5% threshold.

The statistical analyses carried out may be modified based on distributions observed and test assumptions. For all statistics, the level for significance will be set at *p*<0.05. Summary statistics will be prepared with means and standard deviations considered for normally distributed outcomes or median and interquartile range for non-normally distributed outcomes, as appropriate.

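### Fisher's exact test is valid here but conservative at 20 to 30 participants; Boschloo's exact test plus an exact interval for the risk difference would be a cheap improvement

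*Protocol article*

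**What the plan says.** The protocol names Fisher's exact test in three places under Statistical methods.

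- Primary outcome—adverse events: an "exact test will be used to compare the proportions of people in sham vs. rTMS who experience any treatment-emergent AEs".
- Protocol compliance: an "exact test to compare sham and rTMS proportions of participants that are compliant", against those who are not.
- MRI: the proportion with new or enlarging lesions at the "post-intervention time point will be compared between sham and rTMS using a" Fisher's exact test.

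The nominal level is common to all analyses: "For all statistics, the level for significance will be set at" p<0.05. Sidedness is not stated.

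On size, Sample size {14} says "Thirty participants in total will be recruited", and "The sample size of 30 participants has been selected based on the safety and exploratory nature of the study". No power or expected rate of any adverse event is given. Sequence generation {16a} says "We will use an allocation ratio of 2:1", stratified by sex in blocks of 6. Trial status reports that "recruitment has now been closed at 20 participants", without arm numbers, and that no intervention comparison had been analysed at submission.

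The Primary outcomes section sets a clinically acceptable difference of 10% for adverse reactions. It cites reference rates from depression trials: headache 16% sham versus 28% rTMS, and scalp pain 15% sham versus 39% rTMS.

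**The concern.** Fisher's test conditions on both margins of the 2×2 table. With few participants, only a few p values are attainable, so the test often cannot get close to its nominal 5% and its true error rate is lower. In an efficacy comparison that caution costs the sponsor. In a safety comparison it works the other way, because a real excess of events on rTMS is less likely to be flagged than the stated 5% level suggests. Exact unconditional tests keep the error rate at or below 5% and use more of it.

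A second point is linked. The protocol gives a 10% margin for adverse reactions, but the only named analysis of the primary outcome tests for any difference at all. A p value from such a test, by whatever method, does not say whether the excess is within 10 percentage points.

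**Working it through.** The protocol states no power or true error rate, so there is no figure to reproduce.

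**Inputs.** Level 0.05 (protocol), taken as two-sided (assumption). Arms 20:10 as planned. For N = 20 the split is assumed. Blocks of 6 within two sex strata can leave two incomplete blocks, which allows anything from 12:8 to 16:4; 13:7 is closest to 2:1. No dropout.

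**Method.** Let *a* of *n*₁ rTMS and *b* of *n*₂ sham participants have an event, and let *R* be the set of tables that a test rejects.

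- Power = Σ over (*a*, *b*) in *R* of Bin(*a*; *n*₁, *p*₁) × Bin(*b*; *n*₂, *p*₂).
- True size = the maximum of the same sum with *p*₁ = *p*₂ = *p*, over *p* from 0 to 1.
- Fisher: *R* = tables with Fisher p ≤ 0.05.
- Boschloo: *R* = tables with Fisher p ≤ *c*, where *c* is the largest cut-off that keeps true size ≤ 5%.

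All tables were enumerated for each split.

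| rTMS:sham | Fisher max. size | Boschloo max. size |
|---|---|---|
| 20:10 | 3.3% | 4.1% |
| 12:8 | 2.3% | 4.3% |
| 13:7 | 2.1% | 4.2% |
| 14:6 | 3.2% | 4.0% |
| 15:5 | 2.5% | 3.9% |
| 16:4 | 1.5% | 3.9% |

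In every split, each table that Fisher rejects is also rejected by Boschloo, so Boschloo cannot have less power at any pair of true rates.

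**One table by hand (13:7).** Take 6/13 events on rTMS and 0/7 on sham. With 6 events in 20, there are C(20,6) = 38,760 equally likely arrangements. Those as unlikely as this one or more so are C(13,6) = 1,716 (*b* = 0), C(7,5) × 13 = 273 (*b* = 5) and C(7,6) = 7 (*b* = 6). Fisher p = (1,716 + 273 + 7)/38,760 = 0.051, which is not significant. Boschloo's cut-off at 13:7 is a Fisher p of 0.062, so it rejects this table while its own size is 4.2%. The same holds for 9/13 versus 1/7 (Fisher p = 0.057).

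**Power, Fisher / Boschloo.**

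| rTMS vs sham | 20:10 | 13:7 |
|---|---|---|
| 70% vs 20% (assumed large effect) | 66% / 75% | 41% / 57% |
| 39% vs 15% (scalp-pain rates) | 18.5% / 18.8% | 7% / 14% |
| 28% vs 16% (headache rates) | 4.2% / 4.2% | 1.6% / 4.1% |

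For 70% versus 20%, the result at other splits of 20 is 49% / 59% at 12:8 and 51% / 53% at 14:6. The size of the gain therefore depends on a split that the protocol does not report.

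**The 10% margin.** As a rough guide, take 15% on sham and 25% on rTMS (the scalp-pain sham rate plus 10 points). The Wald half-width of a 95% interval is 1.96 × √(0.25×0.75/*n*₁ + 0.15×0.85/*n*₂). At 20:10 this is 1.96 × √(0.009375 + 0.01275) = 29 points. At 13:7 it is 1.96 × √(0.01442 + 0.01821) = 35 points. The interval shows this uncertainty directly, whereas a non-significant p value hides it.

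**The case against.** The strongest reply is that nothing in the plan is wrong. Fisher's test is standard in small trials, its error rate never exceeds the stated 5%, and the protocol claims neither a power nor a true size that the calculation contradicts. That stands, and it is why this is an improvement and not an error.

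It is also fair that the change does little for the effects the protocol has in view. At the planned 20:10, the gain at the cited headache and scalp-pain rates is between 0 and about 0.4 points (18.5% to 18.8% at most, after rounding). At 13:7 it is about 2 to 7 points, and power remains at or below 14%. The protocol also expects lower rates of these reactions than those trials saw. The large gains belong to large effects.

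Nor does safety rest on this p value alone. Serious events and events leading to discontinuation are tabulated or listed, and an independent neurologist reviews serious events.

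Finally, replacing a published primary test after recruitment has closed is not free. It must be documented as made before any comparison was seen. At submission that was still possible.

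**Conclusion.** Fisher's test is valid but conservative here: at most 3.3% true size at 20:10, and 1.5% to 3.2% at N = 20 depending on the split. Boschloo's test stays within 5% and is never less powerful, so it is the better default among exact tests. The benefit ranges from nothing to about 16 points in the scenarios tabulated. These figures assume two-sided testing, no dropout and, at N = 20, an arm split that the protocol does not give.

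A reader might infer three stronger things that the documents do not support.

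- That the true error rate is about 2%. This fits 13:7 and some other splits of 20, but not the planned 20:10, and 13:7 is only an assumption.
- That Boschloo's test uses the full 5%. It stays below that, at 3.9% to 4.3%.
- That Fisher's test is why the trial might miss a harm. At the protocol's reference rates no test is well powered with 20 to 30 participants.

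The more useful half of the change is the confidence interval, because the protocol sets a 10% margin that a test of no difference cannot address.

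**What to change.** Before database lock, state in the statistical analysis plan:

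1. Two-sided Boschloo's exact test for the adverse-event, compliance and new or enlarging lesion comparisons, with Fisher's p value shown beside it.
2. An exact unconditional 95% confidence interval for the rTMS minus sham risk difference for each of these. The interval for adverse reactions (events judged related) is read against the 10% in the Primary outcomes section, and a non-significant p value is not taken as showing that the excess is within that margin.
3. The date of the change, and that no comparison between arms had been analysed when it was made.

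The cost is a few lines of wording and standard software. The downsides are a less familiar test name and a documented departure from the published test. If the team prefers to keep Fisher's test as published, adding the interval alone would secure most of the value.
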